### Regular study end

The estimated accrual period is 24 months. The regular end of the treatment period for each patient is three weeks after initiation of radiation therapy (after 16 fractions). The regular end of study participation for each patient is after a follow up period of 12 months.

### Prematurely study termination

Reasons for premature termination of the entire study are unacceptable risks and toxicities as specified by the Safety Board as occurrence of a toxicity of grade 5, of 2 consecutive grade 4 toxicities or 5 consecutive grade 3 toxicities judged to be definitively associated with study therapy. Other reasons are new scientific findings during the period of study that require a different treatment. Individual reasons for premature study termination are serious events or a patient’s request.

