## Introduction

The advantage of radiation therapy with particles is based on the particular physical and biological characteristics of ions. Protons and carbon ions as compared to photons lead to an improved conformal dose distribution, which allows a better sparing of surrounding tissue and concurrent dose escalation in the tumor. Carbon ions seem to have an additional biological advantage due to their higher biological effectiveness in contrast to protons [1-3]. Complex double-strand breaks of the DNA seem to be the reason [4,5]. Therefore, heavy ions provide a promising treatment option for tumors with lower radiosensitivity and critical location. Increased cure rates and low toxicity of a particle therapy are the expected results in tumors with low alpha/beta values. Chordomas, as a typical example, are rare malignant tumors (1-4% of all malignant bone tumors). This slow growing tumor arises from embryonic remnants of the chorda dorsalis. The incidence rate is 0.1/1,000,000 [6]. Historically, a higher incidence of sacral chordomas than skull base chordomas was assumed [7]. However, published SEER data of 400 patients with chordoma show an equal distribution with 32% on the skull base, 32.8% spinal and 29.2% in the sacral region [6]. The histological classification is divided into three types: conventional (most common type), chondroid and dedifferentiated [7-9]. The quality of surgical margin is the most important factor for local control and survival [10-12]. An adequate safety margin can only be achieved in about 50% of the patients with sacrococcygeal chordomas [11-13]. Therefore, after R1/R2 resection the local recurrence rate is about 100% without any additional therapy. Fuchs et al. could show a significantly different time of local control between patients with radical resection and subtotal resection [11]. Nevertheless the data of Park et al. indicate a large difference in local failure rate between patients irradiated for primary versus recurrent sacral chordomas after surgery. Hence, an adjuvant high-dose radiotherapy for acceptable control rates is required after complete resection [14]. High conformal techniques help to achieve a safe dose escalation. As mentioned above, due to their physical properties ions provide the best conditions. Proton therapy is the current international standard in irradiation of skull base chordomas. The results of the Loma Linda University Medical Centre, the Massachusetts General Hospital in Boston, and the PSI in Villingen (Switzerland) show excellent control rates for proton therapy [15-17]. In the GSI in Darmstadt, we irradiated with carbon ions by now about 300 patients with skull base chordoma/chondrosarcoma. Published data of the first 96 patients that were treated at the GSI displayed 3- and 5-year local tumor control rates (LC) of 81% and 70% with overall survival (OS) rates of 92% and 89%, respectively [18]. Currently, there is a randomized phase III trial under recruitment, testing protons against heavy ions in patients with skull base chordoma in our department [19]. In addition, over 70 patients with sacral chordoma were treated with carbon ion in our heavy ion therapy center (HIT) between 2010 and 2012. Furthermore, in chordomas of the sacral region surgical resection is still the standard therapy and the extent of surgical resection is important for the local disease free interval [11]. Due to the size, proximity to neurovascular structures and the complex anatomy of the pelvis a complete resection with adequate safety margin is often difficult to realize. A radical resection, especially above S2, often leads to urinary and bowel incontinence as well as motoric/sensoric dysfunctions [20,21]. An adjuvant/additive treatment with charged particles can increase the local control rate after surgery [14,22,23]. Radiobiological considerations lead to low alpha/beta value for chordoma (the tissue-specific constant that indicates the sensitivity of the tissue for the probability of late toxicity by increasing the single dose). The alpha/beta value for chordoma cells (2 Gy) [24] is significantly lower for other organs at risk (bladder alpha/beta 4.0 Gy; rectum alpha/beta 3.9 Gy). Thereby, a higher single dose can be used, treating the chordoma cells more effectively without increasing the risk of side effects. A Japanese trial with primary carbon ions irradiation without previous surgery confirmed this radiobiological model [25]. The data show an excellent control rate after primary radiotherapy with carbon ions in patients with inoperable sacral chordoma. 95 patients were treated with 16 fractions carbon ions over 4 weeks with a total dose of 52.8 GyE up to 73.6 GyE (70.4 Gy median TD). The fraction dose therefore was 3.3 GyE up to 4.6 GyE (4.4 Gy median SD) applied four times a week. At 5 years, the OS rate and LC rate were 86% and 88%, respectively. The rate of acute/late skin toxicity grade 3 and higher was 6.3%. Only one patient (1%) showed transient rectal bleeding 20 months after therapy (Grade II). The published study with ion irradiation of sacral chordoma was conducted using a passive beam modulation. A further development of the ion irradiation is the active beam delivery using raster-scanning method. The advantage of this method is especially the lower neutron production when used in our department. As a result of the higher neutron production the passive beam modulation shows no advantage over IMRT regarding secondary cancer risk [26]. Until now there have been no published data of hypofractionated irradiation with protons in sacral chordoma. Therefore, this is the first randomized Phase II trial protocol with hypofractionated carbon ion versus proton treatment in patients with sacrococcygeal chordoma in a single institution open for recruitment since January 2013.

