### Assessment of efficacy parameters

#### Toxicity and safety

To evaluate the toxicity, this study will use the International Common Terminology Criteria for Adverse Events (CTCAE) version 4.0 for toxicity and adverse event reporting. Safety and toxicity of the study treatment will be evaluated by clinical examination as well as imaging studies (MRI or CT). At enrollment, each patient will be asked for his medical history and pass through a basic clinical examination with regard to already existing problems. During radiation therapy the patient is monitored continuously. Once a week, a meeting with the investigator will take place in order to record the adverse effects. At the end of the treatment and in the follow up visits the clinical symptoms and toxicity will be documented again. Follow up visits are planned for 6–8 weeks, 4 months, 8 months and 12 months after irradiation. A safe feasibility exists, if no grade 3 or higher toxicity has occurred (including toxicity-related death, Grade 5) from start of radiation until 12 months after the end of therapy, and if the therapy was not canceled due to any toxicity (grade 1–4). It will be evaluated be the respective portion of patients denoted SFR (safe feasibility rate).

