### Statistical consideration and analysis

With the present study, basic data are obtained for hypofractionated carbon ion radiation and proton radiation in sacral chordoma patients to be used for planning a confirmative randomized phase III trial comparing proton and carbon ion irradiation. At present, hypofractionated carbon ion radiation is considered as the standard, supported by data already existing in Japan. However, the treatment in Japan was performed without using the raster-scanning method. Nevertheless, these data can serve as historical control for the planning of this pilot study and provide the framework for the assessment of safety and feasibility of the proposed study treatments using the SFR as endpoint. Each of the planned study treatments (Arm A: protons or arm B: carbon ions) will be tested separately for this endpoint in a non-inferiority study design in comparison with that (historical) control. The comparative evaluation of favorable toxicity is assessed in an exploratory comparison by comparing the SFR of both arms. With these results, a further trial is then planned to evaluate the efficacy and safety of hypofractionated irradiation with carbon ions or protons with active beam delivery of sacral chordoma. Consequently, the following two questions will be considered in preparation for the subsequent confirmatory study:

a) Is the toxicity of carbon ion irradiation (Arm B) non-inferior to the current standard?

b) Is the toxicity of the proton irradiation (arm A) non-inferior to the current standard?

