The number of patients to be recruited is calculated separately for each arm with an assumed standard toxicity rate of 7% (Grade 3–5 NCI-CTC AE Tox, including premature termination). Thus, the safety rate is set to 93% accounting for the Japanese results, where a toxicity of grade 3 or higher in 6.3% of patients was found [25]. Identical non-inferiority limits for toxicity and statistical error probabilities (type I error = type II error = 10%) are selected for each of the two arms. Randomization is used to obtain a balanced patient population in both groups and based on permuted block randomization stratified for the CTV size (> or ≤ 1 L). Comparison between the two arms will be carried out as a secondary comparison. The non-inferiority of each of the two arms compared to the standard is assessed in a one-sided hypothesis test: H0: SDR <93% versus H1: SDR > = 93% - DELTA. For the proposed pilot trial a non-inferiority limit (DELTA) of 13% is assumed. To test the efficacy and safety of the treatment, 45 evaluable patients per arm are required to reach a power of 90% (type II error = 10%) at a significance level 10% (type I error). Non-inferiority is denied, if safe feasibility is possible in less than 40 patients (i.e. if more than 5 of the 45 (90%) evaluable patients show toxicity. Each of the two tests is to be tested with a power of 90% (power = 90%, beta = 0.1) in a one-sample binomial test. Confidence intervals of the SFR are calculated as describing parameters. With an estimated drop out rate of approximately 10%, 50 patients should be included in each arm in order to obtain 45 evaluable patients. This sample size calculation is based on the PASS software of 2005 and the method of Blackwelder (1982) for non-inferiority trials [27]. The secondary endpoints OS and LPFS will be analyzed via descriptive methods of censored survival times (Kaplan Meier method).

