### Data safety monitoring board (DSMB)

An independent Data and Safety Monitoring Board (DSMB) will monitor the recruitment, the reported adverse events and the data quality. Based on its review the DSMB will provide the Principal Investigator (PI) with recommendations regarding trial modification, continuation or termination.

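### If consecutive means consecutive patients, the grade 3 and grade 4 stopping runs seldom fire in an arm at 20% toxicity; a DSMB notice at the arm's sixth failure would close the gap cheaply

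*Protocol article*

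**What the plan says.** The section on premature study termination gives toxicity grounds for ending the whole study: one grade 5 toxicity, or a run "of 2 consecutive grade 4 toxicities or 5 consecutive grade 3 toxicities judged to be definitively associated with study therapy". The DSMB section says that an independent board "will monitor the recruitment, the reported adverse events and the data quality", and that it may recommend modification, continuation or termination. Neither section mentions the arms.

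The analysis is by arm. Under Statistical consideration and analysis, each treatment "will be tested separately for this endpoint in a non-inferiority study design in comparison with that (historical) control". The reference toxicity rate is 7% and "a non-inferiority limit (DELTA) of 13% is assumed". The decision limit is a cumulative count: "Non-inferiority is denied, if safe feasibility is possible in less than 40 patients", that is, more than 5 failures among 45 evaluable patients.

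Under Toxicity and safety, a failure of the safe feasibility rate (SFR) is a grade 3 or higher toxicity "from start of radiation until 12 months after the end of therapy", or a treatment cancelled because of toxicity. Toxicity is recorded often: "Once a week, a meeting with the investigator will take place in order to record the adverse effects", and again at the end of treatment and at four follow-up visits.

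**The concern.** The plan judges an arm by its cumulative failures, but its numeric alarm for grades 3 and 4 is an unbroken run, set for the whole study and conditional on definite attribution. An arm can collect many scattered grade 3 events without ever forming a run.

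After its sixth failure an arm can no longer be declared non-inferior on 45 evaluable patients. Whether the board looks at that arm while patients are still being entered then depends on its general review and not on a stated trigger. This matters most for the proton arm, of which the Introduction says: "Until now there have been no published data of hypofractionated irradiation with protons in sacral chordoma".

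**Working it through.** **Inputs**
- Reference toxicity 7%, margin 13 points, 45 evaluable and 50 enrolled per arm, limit 40 of 45 (Statistical consideration and analysis).
- Toxicity at the margin: 100% − (93% − 13%) = 20%.
- Accrual 24 months, treatment about three weeks (Regular study end). The failure window runs to 12 months after therapy, so to about 12.75 months from start.
- Assumed: share of grade 4 among grade 3–4 events 0 to 40%. The 40% is the 3:2 split of skin toxicity reported in the Discussion for the Japanese series, where such events arose at 70 GyE or more, against 64 GyE here. Attribution, block size and time to toxicity are also assumptions. Grade 5 is not modelled.

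**1. The plan's own limit.** With X binomial on 45 patients, P(X ≥ 40) is 0.0902 at a success rate of 0.80 and 0.9077 at 0.93. The stated 10% error and 90% power are reproduced.

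**2. The runs, counted over consecutive patients of one arm.** A run of r events of probability p among n patients has probability of at most p^r × [1 + (n − r)(1 − p)].
- Grade 3 only, p = 0.20, r = 5, n = 50: 0.00032 × (1 + 45 × 0.80) = 0.0118.
- Grade 4 at a 40% share, p = 0.08, r = 2: 0.0064 × (1 + 48 × 0.92) = 0.289, an upper bound; the exact value is 0.254.

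The exact Markov-chain results for either run in an arm of 50 at 20% toxicity are:

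| Grade 4 share | All events judged related | Half judged related |
|---|---|---|
| 0 | 1.2% | 0.04% |
| 10% | 2.6% | 0.5% |
| 40% | 25.5% | 7.3% |

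If the run is counted across both arms, with the other arm at 7%, the range is 0.2% to 19% with alternating entry and 0.2% to 24% with permuted blocks of 2 to 6.

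**3. The by-arm count.** P(6 or more failures among 45) is 91.0% at 20% toxicity and 9.2% at 7%. If all 50 enrolled patients are counted, the 7% figure becomes 13.5%. With both arms at 7%, at least one arm reaches six in 1 − (1 − 0.0923)² = 17.6% of trials.

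**4. What the count adds to the runs.** At 20%, an arm has its sixth failure within 45 patients and neither run fires at any point among those 45 in 90% of cases (no grade 4), 89% (10% share) or 68% (40% share).

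**5. Whether the notice comes in time.** Take uniform entry over 24 months, and let f be the share of failures seen by month 24. The chance of a notice before accrual ends is P(Bin(45, 0.20f) > 5).

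| Failures appear | f | Notice before accrual ends | Median of 45 still to enter, all arms |
|---|---|---|---|
| Within 3 months | 1 − 1.5/24 = 0.9375 | 87% | 14 |
| Evenly over the window | 1 − 6.375/24 = 0.734 | 66% | 4 |
| Only at 12 months | 1 − 12.75/24 = 0.469 | 24% | 0 |

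The medians are simulated and count an arm without a timely notice as zero. Among arms whose notice does come before accrual ends, they are 15, 9 and 4.

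**The case against.** **The board already watches adverse events, and a charter may hold a by-arm trigger.** Both parts are fair. A reader might infer that a failing arm would go unseen; the document does not support that, since an independent board monitors reported events and can recommend termination. What stands is narrower: the article states its toxicity criteria in numbers, and those for grades 3 and 4 respond poorly at the margin.

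**The runs are an emergency brake.** Also fair. The 20% is the boundary of the final test, not a declared stopping threshold, and nothing says that the runs should detect it. A reader might call the rule an error; it is better described as unconnected to the by-arm limit that the plan sets.

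**The text speaks of consecutive toxicities, not patients.** If uneventful patients do not break the run, it fires in about 75% to 98% of arms of 50 at 20% (grade 4 share 0 to 50%). So a flat claim that the runs seldom fire would be too strong. But the same reading would stop about 55% to 84% of trials with both arms at the accepted 7%, which makes it unlikely. The word needs defining either way.

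**The grade 5 limb is left out.** True. It stops the study on one event, and the document gives no grade 5 rate. The figures describe the two runs and not the complete rule.

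**The sixth failure is mostly a futility signal and may come late.** This stands in part. A saving of about 15 patients per arm is a tempting reading, but it holds only for early toxicity and a notice that arrives before accrual ends.

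**Conclusion.** The point holds as a design improvement and leaves the analysis untouched. On the consecutive-patient reading, and with the grade 5 limb set aside, the runs fire in about 1% to 26% of arms of 50 at 20% toxicity when all events are judged related, and in fewer when attribution is stricter. The width of that range comes almost wholly from the grade 4 share, which the document does not fix. The plan's own by-arm limit is crossed in 91.0% of arms at that rate, and no stated trigger brings the crossing to the board. The change is worth making because it uses a limit and data that the plan already has. Confidence is medium: it rests on the reading of one word and on an unknown grade mix, and the benefit shrinks if toxicity appears late.

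**What to change.** Keep the grade 5 limb and both runs, and add to the termination and DSMB sections:

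> Consecutive means consecutive treated patients. Grade 3–5 toxicities and toxicity-related discontinuations, as defined under Toxicity and safety, are counted cumulatively by patient within each arm. When an arm records its sixth such failure among evaluable patients, the DSMB is notified promptly and reviews that arm; the study does not stop automatically. Each DSMB listing shows, by arm, the patients treated, the failures and the acute grade 3–4 events.

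The counted failure has to be named because the abstract and the primary-endpoint section count discontinuation for any reason, whereas Toxicity and safety counts only toxicity-related cancellation. The acute-event column is needed because failures accrue for 12 months after therapy and the notice may come late.

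Cost: a few sentences and a by-arm listing from data already recorded. Because the notice does not stop the study, the sample size, error rates and decision limit do not change. The downside is the extra board review in 9.2% of arms at 7% toxicity, or 13.5% if all 50 enrolled patients are counted.

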
## Methods and design

### Primary objectives/endpoints of this study

The primary objective of this trial is the evaluation of safety and feasibility of hypofractionated irradiation in patients with sacrococygeal chordoma using ions (protons or carbon ions) in raster scan technique for primary or additive treatment after R2 resection. The evaluation is based on as primary endpoint defined as the proportion of patients treated without Grade 3–5 toxicity (NCI-CTC-AE) up to 12 months after treatment and/or without discontinuation of the treatment for any reason.

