### Quality of life

The quality of life (QoL) is detected using the EORTC QLQ-C30 questionnaires that are filled in by the patient before treatment, at the end of treatment and 12 months after irradiation. The evaluation of the questionnaires is carried out for the individual patients after the complete collection of all data. To determine a change in QoL it will be compared with the pretherapeutic QoL for each patient in both arms. QoL will be compared between the two arms of the study after end of radiation and at end of study for the patients. For the analysis of the EORTC questionnaires the EORTC QLQ-C30 Scoring Manual will be used.

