### Overall survival (OS)

Overall survival is a secondary endpoint of the study. The duration of survival is the time interval between beginning of radiotherapy and the date of death due to any cause or to loss to follow-up (censored observation). Patients not reported dead or lost to follow-up will be censored at the date of the last follow-up examination (Figure 3).

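### Serious events are listed as a reason to end an individual patient's study participation, so follow-up may stop for reasons linked to outcome

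*Protocol article*

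**What the plan says.** All references are to the protocol article.

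- *Prematurely study termination*: after the trial-level stopping criteria, one sentence covers the single patient: "Individual reasons for premature study termination are serious events", or a request by the patient. It does not define a serious event or say what data collection follows.
- *Regular study end* keeps two endings apart. For treatment: "The regular end of the treatment period for each patient is three weeks after initiation of radiation therapy (after 16 fractions". For participation: "The regular end of study participation for each patient is after a follow up period of 12 months".
- *Toxicity and safety*: the SFR requires that no toxicity of grade 3 or higher occurs "from start of radiation until 12 months after the end of therapy", and that therapy is not cancelled because of toxicity. *Primary objectives/endpoints of this study* words the endpoint differently: "up to 12 months after treatment and/or without discontinuation of the treatment for any reason".
- *Quality of life*: after baseline, the questionnaire is completed "at the end of treatment and 12 months after irradiation", and the arms are compared at both of these times.
- *Overall survival (OS)*: "Patients not reported dead or lost to follow-up will be censored at the date of the last follow-up examination". The same section also treats loss to follow-up as a censored observation.
- *Statistical consideration and analysis*: 45 evaluable patients per arm, 50 included to allow for about 10% drop-out. Non-inferiority is denied with fewer than 40 safe patients. OS and LPFS are described by Kaplan-Meier.

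**The concern.** Because the article gives treatment and participation separate endings, the plain reading of the individual rule is that a serious event can take a patient out of the study, not only off irradiation. The reason for leaving is then related to what the trial measures.

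Three things are at stake. First, QoL at 12 months, LPFS and OS all need observation after the event. If patients who do worse leave, the questionnaire mean comes from a selected group and the Kaplan-Meier curves may be informatively censored. Second, later worsening of a toxicity would not be graded at the planned visits, so the safety description loses detail. Third, the article does not define who is evaluable. A patient who leaves for a serious event could be scored as an SFR failure or absorbed into the 10% drop-out allowance, and the primary test behaves very differently in the two cases.

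**Working it through.** **1. The plan's own figure.** Inputs from *Statistical consideration and analysis*: standard SFR 93%, margin 13 points, hence a limit of 93% − 13% = 80%; one-sided type I error 10%; power 90%; pass with at least 40 of 45. By the exact binomial:

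- P(X ≥ 40 | n = 45, p = 0.80) = 0.0902
- P(X ≥ 40 | n = 45, p = 0.93) = 0.9077

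Forty-five is the smallest n that meets both error limits, and 45 / 0.90 = 50. The design reproduces.

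**2. When the SFR is safe.** Take a serious event that is a toxicity of grade 3 or higher, or that cancels therapy for toxicity. The patient is an SFR failure at that moment, and nothing observed later can change this. If the patient is scored so, the type I error stays at 9.0%.

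The status is not settled for a serious event that meets neither condition. If therapy is stopped for a reason other than toxicity, the two endpoint wordings disagree on whether this is a failure. If the event falls after treatment, leaving the study means that later toxicity up to 12 months is not seen.

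**3. When the SFR is exposed.** Let a share q of failures leave and be treated as non-evaluable. The article gives no q, so a range is shown. With true SFR p, the apparent SFR among evaluable patients is

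p / [p + (1 − p)(1 − q)].

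At p = 0.80, with 45 evaluable patients:

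| q (assumed) | Apparent SFR | P(at least 40 of 45) |
|---|---|---|
| 0 | 0.800 | 9.0% |
| 10% | 0.80/0.98 = 0.816 | 14.2% |
| 25% | 0.80/0.95 = 0.842 | 26.5% |
| 50% | 0.80/0.90 = 0.889 | 61.6% |

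At this SFR, 0.20 × 50 = 10 failures are expected per arm. The four rows therefore correspond to about 0, 1, 2.5 and 5 dropped patients. The last row would use the whole drop-out allowance and is an extreme.

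A single-arm example: of 50 patients, 40 are safe, 5 are recorded failures and 5 leave after a serious event that meets the failure definition. Leaving them out gives 40/45 = 88.9%, p = 0.090 against 80%, a pass. Counting them as failures gives 40/50 = 80.0%, p = 0.58.

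**4. Secondary endpoints, upper-bound illustration.** Assume that serious events occur at the grade 3–5 rate and that every such patient leaves. Between the planned 7% and the limit of 20%, that is 0.07 × 45 = 3.2 to 0.20 × 45 = 9 patients per arm. If they would have scored 20 points lower on a QLQ-C30 scale (assumption), the arm's 12-month mean is overstated by 0.07 × 20 = 1.4 to 0.20 × 20 = 4 points. In the comparison of arms only the difference matters: zero if both arms lose the same share, and 4 − 1.4 = 2.6 points at the two extremes.

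**The case against.** The case on the other side has four parts.

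- **The sentence permits; it does not compel.** It lists reasons and does not say that every serious event removes a patient or that data collection then stops. This stands. A reader might infer that these patients do leave and that their outcomes do go unobserved. The text supports only that this may happen, which is why the figures in step 4 are upper bounds.
- **An article condenses a fuller protocol.** Rules for follow-up after withdrawal are often left to that document. This would answer a complaint about silence. Here the article states a rule, and states it for the study rather than for treatment, so it does not dispose of the point.
- **The primary endpoint is largely protected.** A reader might infer that 12-month toxicity is lost for the SFR. For qualifying toxicities it is not: the failure is fixed when it occurs, and worsening from grade 3 to grade 4 or 5 does not alter it. The exposure depends on how evaluable is understood.
- **OS is not censored at a serious event by any stated rule.** This stands. Censoring is at loss to follow-up or the last examination, and a fatal serious event is itself an OS event. Early censoring would arise only indirectly, because visits stop.

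Two stronger readings should be set aside. One is that the arm with more serious events would look better on every remaining measure: the SFR would still count its failures if they are scored, and the QoL bias between arms is only a difference. The other is that one missed death would remove most of the OS signal. Under a constant hazard and the 86% five-year OS of the cited Japanese series, 50 × (1 − 0.86^(1/5)) ≈ 1.5 deaths per arm are expected in 12 months. OS is descriptive and would say little at that size whatever the withdrawal wording. Nor does the article say that adverse-event reporting to the DSMB would cease.

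**Conclusion.** The concern holds in limited form. The individual rule, as written, allows study participation to end because of a serious event, and nothing in the article keeps the patient in follow-up. Outcome-related loss of 12-month QoL, LPFS, OS and later toxicity detail is therefore possible. Its extent cannot be known from the document; 3 to 9 patients per arm and 1.4 to 4 QoL points are an upper-bound illustration under the stated assumptions.

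The primary test keeps its exact 9.0% type I error if qualifying events are scored as failures. It becomes anti-conservative only if such patients are placed among the drop-outs: 14.2% or 26.5% when 10% or 25% of failures are dropped, both shares being assumptions. This should be corrected, but it is a matter of wording and patient accounting. The sample size itself is sound on the plan's own inputs.

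**What to change.** Reword the individual-patient sentence under *Prematurely study termination* to say that:

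1. A serious event does not end study participation. Whatever is decided about irradiation, on which this point takes no position, the patient stays in the scheduled follow-up (toxicity, MRI, QLQ-C30, vital status) to 12 months. Only withdrawal of consent to follow-up ends it.
2. OS and LPFS are not censored at the serious event.
3. A patient who nevertheless leaves for a serious event that meets the SFR failure definition stays in the SFR denominator as a failure and is not replaced as a drop-out.

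For item 3 to work, the two wordings of treatment discontinuation (for any reason, or for toxicity only) need to be reconciled. The cost is a few sentences. The visits at 6–8 weeks and 4, 8 and 12 months are already planned for every patient, and the sample size does not change. The downside is some follow-up effort in ill patients.
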